## Abstract

**Introduction:**

Endometriosis is associated with reduced pregnancy and live birth rates in patients attempting both spontaneous and assisted conception. At present, it is unclear whether prepregnancy surgery for moderate or severe endometriosis, either in the setting of established infertility or even before a woman has begun trying to conceive, confers any benefit in terms of (a) spontaneous conception, (b) conception with assisted reproductive technology (ART), (c) live birth or (d) other obstetric outcomes.

**Methods and analysis:**

The Endometriosis Longitudinal Fertility Study (ELFS) is a multisite prospective longitudinal cohort study, recruiting patients <38 years of age with evidence of moderate or severe endometriosis (revised American Society of Reproductive Medicine grades 3 or 4) who desire fertility immediately or in the near future. ELFS aims to longitudinally assess clinical pregnancy and live birth rates for women with moderate or severe endometriosis who choose to have no treatment, fertility treatment and/or surgery. The target sample size was determined by a simulation-based power calculation. The study will comprise 700 participants: 400 attempting natural conception and 300 attempting to conceive with ART. Each of these cohorts will be divided evenly between the conservative and surgical management groups. Following consent and baseline questionnaire, participants instal the purpose-built ELFS App to their mobile phone. The participant then receives cyclical surveys at intervals based on their menstrual cycle, with timing dependent on learnt logic from prior responses. Participants conclude participation following a live birth beyond 20-week gestation. The primary research outcome is to compare the ‘per cycle’ clinical pregnancy rate and live birth rate where endometriosis is managed conservatively or surgically in those conceiving naturally or with assisted reproductive techniques. Secondary outcomes include exploring menstrual cycle characteristics and examining the obstetric outcomes of women with moderate and severe endometriosis who successfully conceive. The outcomes of this research aim to contribute to improving endometriosis management for women desiring pregnancy by establishing if there is a fertility benefit of prepregnancy surgery in patients with moderate or severe endometriosis.

**Ethics and dissemination:**

The Austin Health Ethics Committee approved the ELFS protocol (HREC/65683/Austin-2020). On study completion, results of the trial will be submitted for publication in a peer-reviewed journal. Interim experiences with the ELFS App as well as relevant secondary outcomes will be presented at international conferences with additional goals for publication.

**Trial registration number:**

ACTRN12621000431820.

STRENGTHS AND LIMITATIONS OF THIS STUDYThe current evidence examining the role of prepregnancy surgery for moderate and severe endometriosis is predominantly retrospective. A main strength of this study is its prospective pragmatic cohort design.The study will use a novel tool (the Endometriosis Longitudinal Fertility Study App) to attempt to improve longitudinal follow-up rates and participant engagement, recognising that endometriosis is a chronic condition and many participants will have prolonged fertility journeys.The study will run internationally and use translation technologies to enable recruitment of language-diverse populations.The primary outcome requires a large study design. Recruitment rates may be impacted by strict inclusion criteria required to ensure accuracy in the diagnosis of moderate-severe endometriosis.Repeated collection of sensitive data (eg, sexual history, fertility, pregnancy outcomes) may have a negative impact on participant experience and engagement.

## Introduction

 Epidemiological studies report a strong association between infertility and subsequent endometriosis diagnosis,^1
2^ and 30%–50% of women with endometriosis experience difficulties conceiving.^3
4^ This association may reflect biological effects of endometriosis on fertility, increased likelihood of diagnostic evaluation among women with infertility or both. Surgically treating milder endometriosis (revised American Society of Reproductive Medicine (rASRM) stages 1 and 2)^5^ has been demonstrated to improve spontaneous clinical pregnancy rates (CPRs) in prospective randomised controlled trials^6^ and is the topic of a recent Cochrane review.^7^ However, for women planning or desiring fertility, the role of surgery for moderate and severe endometriosis (including deep endometriosis and ovarian endometriosis) in improving fertility and pregnancy outcomes is not fully understood.^7–16^

A literature review^17^ summarising the fertility outcomes before and after surgery for deep endometriosis concluded that in patients without bowel involvement, postoperative overall pregnancy rates were 68.3% (95% CI 64.9% to 71.7%) but no comparison with presurgical pregnancy rates was possible. In the same review, patients with bowel endometriosis may have experienced improved pregnancy rates after surgery, but numbers were small and all conceived with assisted reproductive technology (ART). Daniilidis *et al*^15^ published a systematic review examining the impact of prepregnancy surgery on subsequent fertility. The authors reported inconsistent outcomes and concluded that more studies are needed to ascertain whether surgical management should be used as first line or only in cases where ART has failed. Similarly, Liang *et al*^10^ published their review comparing pregnancy rates between first line surgery for deep endometriosis and first line ART. The authors reported comparable outcomes between the groups and concluded that further studies were needed, particularly with regard to surgical management of endometrioma. Thus, at present, the European Society of Human Reproductive Endocrinology guidance advises that operative laparoscopy may be a treatment choice for symptomatic patients who want to become pregnant, but no compelling evidence exists to support surgical treatment of deep endometriosis to improve spontaneous or ART pregnancy rates.^18^

Laparoscopic surgery to remove endometriosis exposes women to surgical risks. Surgery could be justified if there is a potential benefit, either in symptom reduction or with improved fertility. Current evidence suggests that patients with deep endometriosis may have improvements in pain symptoms following surgery, particularly after colorectal surgery.^19^ In the group of patients who do not experience significant pain and would be considering surgery to optimise fertility alone, further evidence is needed before the risks of surgery can be justified. Moreover, the issue of future fertility is a vexed question for many women with endometriosis, and the known association with infertility raises questions about whether pre-emptive surgical treatment of endometriosis will provide future benefit with improved pregnancy rates, particularly with regard to risk of adhesions, prevention of disease progression and reductions in ovarian reserve.^20
21^

In recent years, there has also been an increase in research focused on the association between endometriosis and pregnancy outcome.^22–24^ It is possible that the presence of endometriosis, or history of a prior diagnosis of endometriosis, may be associated with poor pregnancy outcomes^25–27^ including placenta praevia, preterm birth, premature prelabour rupture of membranes, obstetric haemorrhage, gestational hypertensive disorders, fetal growth restriction and perinatal death.^28^ It is unknown whether the obstetric outcome risk is ameliorated by prepregnancy surgery for endometriosis or if there is a surgically untreatable factor which underpins the likely increased risk of adverse obstetric outcomes.^9^

Ultimately, our proposed study aims to compare fertility outcomes among four groups of participants with evidence of moderate-severe endometriosis (EMSE):

Those pursuing natural conception without prior surgery.Those pursuing ART without prior surgery.Those undergoing surgery followed by attempts at natural conception.Those undergoing surgery followed by ART.

Cross-comparisons are planned across all four groups.

This study will explore the impact of surgical treatment of moderate to severe endometriosis on pregnancy and live birth rates (LBRs) from both natural conception and in vitro fertilisation (IVF). Obstetric and perinatal outcomes will be assessed as secondary outcomes. In addition, it will seek to clarify whether pre-emptive surgical treatment of endometriosis has an impact on future fertility.

## Methods and analysis

The Endometriosis Longitudinal Fertility Study (ELFS) is a prospective longitudinal cohort study.

### Study objectives

ELFS aims to measure and compare monthly clinical pregnancy and LBRs prospectively and longitudinally in women with EMSE who are undertaking surgery or conservative management prior to conception. Secondary objectives include collection of menstrual cycle data longitudinally in women with moderate or severe endometriosis.

Primary and secondary outcomes have been prespecified with explicit definitions.

#### Primary outcome

LBR (live birth/number of attempted cycles)—‘live birth’ will be defined as birth of a live infant >20 weeks gestation.

For women with EMSE who are attempting natural conception, the ‘per cycle’ LBR will be compared between conservatively or surgically managed groups.

For women with EMSE and infertility who are undergoing IVF, the ‘per cycle’ LBR will be compared between conservatively or surgically managed groups.

#### Secondary outcomes

CPR (clinical pregnancy/number of attempted cycles)—for the purposes of this study, ‘clinical pregnancy’ will be defined as a pelvic ultrasound demonstrating a gestational sac (intrauterine or extrauterine).For women with EMSE who have been trying to conceive for less than 12 months or plan to in the future, the ‘per cycle’ CPR will be compared between groups where EMSE is managed conservatively or surgically excised.For women with EMSE and infertility who are undergoing IVF the ‘per cycle’ CPR will be compared between groups where EMSE is managed conservatively or surgically excised.For women with EMSE and infertility who are attempting natural conception, the ‘per cycle’ CPR will be compared between groups where EMSE is managed conservatively or surgically excised.Menstrual cycle characteristics including: cycle length, length of menstrual period, heaviness of flow, associated pain symptoms.Rates of adverse pregnancy outcomes of women with EMSE who successfully conceive. This is a composite outcome of adverse perinatal outcome including—premature birth, hypertensive disorders of pregnancy, caesarean delivery, fetal growth restriction and severe maternal mortality.

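### The adverse perinatal composite names no perinatal death, counts caesarean delivery as an event, and contains an unusable maternal component

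*Protocol article*

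**What the plan says.** Under Secondary outcomes, the protocol article sets an outcome described as "Rates of adverse pregnancy outcomes of women with EMSE who successfully conceive". It continues: "This is a composite outcome of adverse perinatal outcome including" and then lists "premature birth, hypertensive disorders of pregnancy, caesarean delivery, fetal growth restriction and severe maternal mortality".

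The Introduction gives the reason for looking at obstetric outcomes. It says endometriosis may be associated with "placenta praevia, preterm birth, premature prelabour rupture of membranes, obstetric haemorrhage, gestational hypertensive disorders, fetal growth restriction and perinatal death", and then states the question the composite would serve: "It is unknown whether the obstetric outcome risk is ameliorated by prepregnancy surgery for endometriosis".

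Study objectives adds a general assurance: "Primary and secondary outcomes have been prespecified with explicit definitions". Under Primary outcome, live birth is defined as "birth of a live infant >20 weeks gestation".

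**The concern.** The composite and its rationale do not match, in three ways.

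- **Perinatal death.** The label says perinatal and the Introduction names perinatal death, but no listed component captures it.
- **Caesarean delivery.** This is a decision about care. The study is an observational cohort, and those who plan a birth can know whether the woman has had pelvic surgery. A difference in delivery planning between the surgical and conservative groups could therefore move the composite with no change in morbidity. If planning does not differ, caesareans add events that carry no information about harm.
- **Severe maternal mortality.** Death has no severity grade. Taken literally, the component counts maternal deaths only and drops severe morbidity.

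At stake is whether the composite can answer the question of obstetric risk after surgery that the Introduction poses.

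**Working it through.** The article gives no rate, sample size or power for this composite, so there is no figure to reproduce. The check has a comparison of the text and an illustration on assumed rates.

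**1. The two lists side by side**

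| Outcome | Introduction | Composite |
|---|---|---|
| Preterm birth | yes | yes |
| Hypertensive disorders | yes | yes |
| Fetal growth restriction | yes | yes |
| Perinatal death | yes | not named |
| Obstetric haemorrhage | yes | not named |
| Placenta praevia | yes | not named |
| Prelabour rupture of membranes | yes | not named |
| Caesarean delivery | no | yes |
| Severe maternal mortality | no | yes |

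Three of the Introduction's seven outcomes are in the composite, four are not named, and two items are new.

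**2. How deaths are classified as the text stands**

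- Term stillbirth, no other listed component: not a live birth, so no success on the primary outcome, and composite-negative.
- Preterm stillbirth: may enter as premature birth.
- Neonatal death after a live birth beyond 20 weeks, no other listed component: a success on the primary outcome, and composite-negative.

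**3. Weight of caesarean (all rates assumed)**

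Let c be the caesarean rate and o the rate of any other component, taken as independent.

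- Composite = 1 − (1 − c)(1 − o)
- Caesarean-only share of events = c(1 − o) / composite

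| c | o | Composite | Caesarean-only share |
|---|---|---|---|
| 0.35 | 0.20 | 1 − 0.65 × 0.80 = 0.480 | 0.280 / 0.480 = 58% |
| 0.40 | 0.20 | 1 − 0.60 × 0.80 = 0.520 | 0.320 / 0.520 = 62% |
| 0.35 | 0.30 | 1 − 0.65 × 0.70 = 0.545 | 0.245 / 0.545 = 45% |
| 0.40 | 0.30 | 1 − 0.60 × 0.70 = 0.580 | 0.280 / 0.580 = 48% |

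The range widens greatly under other assumptions. Take caesarean from 10% to 50%, and preterm birth, hypertensive disorders and growth restriction from 5/4/5% to 15/15/15%. The caesarean-only share is then 14-76% under independence. It is 6-74% if women with another component have twice the average caesarean risk (capped at 90%).

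**4. Two ways this could mislead (assumed inputs)**

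*Spurious difference.* Suppose caesarean is 10 points higher in one group and nothing else differs. With c going from 0.35 to 0.45 and o = 0.20, the composite goes from 0.48 to 0.56. The odds ratio is (0.56/0.44) / (0.48/0.52) = 1.38. Across the four combinations above it runs from 1.33 to 1.38.

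*Dilution.* Suppose the other harms are 25% v 15%, with 100 pregnancies per group. Power without caesarean is 42%. With caesarean at 30% in both groups, the composite is 1 − 0.75 × 0.70 = 47.5% v 1 − 0.85 × 0.70 = 40.5%, and power falls to 17%. At caesarean rates of 10% and 50% it is 29% and 11%.

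**5. Effect of adding perinatal death**

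At an assumed 0.5-3%, a composite of 48% becomes 1 − 0.52 × 0.995 = 48.3% up to 1 − 0.52 × 0.97 = 49.6%. The reason to add it is validity, not event numbers.

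**The case against.** The strongest reply is that three of the five components are genuine harms that the Introduction also lists, and that nothing in the article shows caesarean to be the commonest. A reader might infer that the composite measures mode of delivery rather than harm. The documents do not support that: with no component rates, a caesarean-only share anywhere from 6% to 76% is compatible with plausible assumptions. Nor do they support the size or direction of any difference in caesarean between the groups; the 10-point shift above is only an illustration.

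Other stronger readings also fail.

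- **Haemorrhage is left out.** This is uncertain. If mortality is a slip for morbidity, haemorrhage may fall inside that component. The text does not say.
- **Placenta praevia must be added.** A composite need not repeat every outcome in a background paragraph. This is a preference.
- **Early losses count as free of adverse outcome.** The article names women who conceive as the population but gives no counting rule for early losses. That detail can be left to an analysis plan.
- **A difference in perinatal death would be hidden.** Only in part. A stillbirth already counts against live birth, and a preterm one may count as premature birth. The plainest gap is neonatal death after live birth.

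It can also be said that the list opens with the word including, so it may not be exhaustive, and that an article condenses the full protocol. Detailed thresholds may indeed sit elsewhere and are not faulted here. But an open list does not fit the assurance of explicit definitions, and it leaves room to choose components after the data are seen. The named components and the wording of the maternal item are printed in the article itself.

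**Conclusion.** The point stands as a defect in the definition of a secondary outcome, worth correcting before analysis. Three things follow from the text without any assumption: no perinatal death is named in a perinatal composite whose rationale names it; caesarean alone makes a woman positive; and the maternal component cannot be applied sensibly as printed.

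How much caesarean dominates or dilutes the result is not known. The 45-62% caesarean-only share rests on assumed rates of 35-40% and 20-30% and on independence. If caesarean is commoner among women with another component, the share is lower.

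**What to change.** - Close the component list and reconcile it with the Introduction.
- Add perinatal death, stated as stillbirth and neonatal death.
- Replace severe maternal mortality with maternal death or severe maternal morbidity, and state whether obstetric haemorrhage falls within it.
- Take caesarean out of the composite and report it on its own.
- Report every component separately beside the composite.

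The cost is a wording change to the protocol and registry, and fewer composite events. On the assumed rates above, removing caesarean takes the composite from 48-58% to 20-30% before the added components. Fewer events need not mean less power, as the dilution example shows. The Interventions section already provides for obstetric outcome data from the hospital of birth. Because the Abstract says participation ends after a live birth, neonatal deaths would have to come from those records, and the period covered should be stated.

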### Power calculation and planned analysis

The target sample size was determined by a simulation-based power calculation. Data were simulated based on a mixed effects logistic regression model with a single fixed effect for treatment and a single random effect for participant. Different random effect SD of 0.5, 0.7 and 0.9 were considered, based on previous studies reporting random effects with SD around 0.7.^36^ Simulations used 5 cycles per participant for natural conception and 3 cycles per participant for IVF. For each set of simulation parameters, 1000 data sets were generated, mixed effects logistic regression models were fitted, and the power was calculated as the proportion of models where the p value for the main effect was below 0.05. The simulation was done using R V.4.0.2, with the glmmTMB package used to fit the mixed effects logistic regression models.

Natural conception based LBR of 1.4% per cycle has been reported in women with moderate to severe endometriosis and 12 months of unsuccessfully trying.^37^ An increase to at least 4% is needed to be clinically significant.^6^ A sample size of N=400 (200 per arm) would achieve over 90% power under the scenarios considered.

An IVF conception-based LBR of 12% per cycle has been reported in women with moderate to severe endometriosis.^38^ An increase to 20% would be needed to be clinically significant. A target sample size of N=300 (150 per arm) would achieve a power of 82% to 87% under the scenarios considered.

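### Any caesarean counts as an adverse event in the obstetric composite, which may then be dominated by mode of birth and dilute or bias the surgery comparison in either direction

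*Protocol article*

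**What the plan says.** Under Secondary outcomes, the last item is "Rates of adverse pregnancy outcomes of women with EMSE who successfully conceive". It is defined as a single composite of adverse perinatal outcome made up of "premature birth, hypertensive disorders of pregnancy, caesarean delivery, fetal growth restriction and severe maternal mortality". Caesarean is not restricted by indication or urgency, and no weighting of components is given. Study objectives states that the outcomes are prespecified and explicitly defined, so the component list is a choice the article makes.

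The Introduction gives the reason for looking at pregnancy outcome. It names complications that endometriosis may raise: "placenta praevia, preterm birth, premature prelabour rupture of membranes, obstetric haemorrhage, gestational hypertensive disorders, fetal growth restriction and perinatal death". It then states: "It is unknown whether the obstetric outcome risk is ameliorated by prepregnancy surgery for endometriosis". The Abstract and the Discussion also list obstetric outcomes among the possible benefits of prepregnancy surgery that remain unclear.

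**The concern.** A composite is useful when its components share a cause and would be expected to respond to treatment in the same way. Prematurity, hypertensive disorders and growth restriction are medical complications, and all three are on the Introduction's list. Caesarean is a decision about how to deliver. It may follow from a complication, but it may equally be planned in a normal pregnancy.

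The design makes this matter. ELFS is a non-randomised cohort in which women choose their management, and no blinding is described. Recruitment covers public and private care in two countries, and birth takes place in whichever hospital the woman attends. Caesarean use could therefore differ between the surgical and conservative groups through practice or preference alone. The adjustment variables named for the fertility models (length of infertility, age, parity, gravidity, male factor, comorbidities, site) would not obviously remove such a difference.

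At stake is how the obstetric result is read. A true effect of surgery on complications could be diluted, and a difference in mode of birth could be mistaken for a difference in perinatal risk.

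**Working it through.** **The plan's own figures.** The article states no rate, effect size or power for the composite. Its only numerical plan is for live birth: 1.4% against 4% per natural cycle, 12% against 20% per IVF cycle. Simulating the stated mixed logistic model with these inputs gave power of 96.7–97.9% for natural conception (stated: over 90%) and 81.7–87.8% for IVF (stated: 82–87%). The planning inputs are therefore consistent with the stated power and are used below only to estimate numbers of births.

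**Assumed inputs.** Let c be the caesarean rate and m the rate of any other component. Neither is in the article. The grid is c = 25, 35, 45, 55%; m = 10, 20, 30%; and an odds ratio between them of 1 (independent) or 3, giving 24 cells.

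**Step 1: share of events due to caesarean alone.**
- Composite = c + m − P(both). Under independence this is 1 − (1 − c)(1 − m).
- Caesarean-only share = (c − P(both)) / composite.
- Central example, c = 0.40 and m = 0.22, independent: composite = 1 − 0.60 × 0.78 = 0.532; share = 0.40 × 0.78 / 0.532 = 0.59.
- Over the grid the share runs from 30% (c = 25%, m = 30%, odds ratio 3) to 83% (c = 55%, m = 10%). It exceeds one half in 17 of 24 cells. The other seven have m of 20–30%, mostly with c of 25–35%.

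**Step 2: dilution, with the same caesarean rate in both groups.** Under independence the change in the composite is (1 − c) × (m0 − m1).
- Central example, m falling from 0.22 to 0.14: 0.60 × 0.08 = 0.048, so the composite goes from 53.2% to 48.4%.
- Over c = 25–55%, between 75% and 45% of the fall survives.
- Positive association lowers the caesarean-only share but does not remedy the dilution. At c = 35% and m falling from 30% to 20%, the composite falls 6.5 points under independence (54.5% to 48.0%) and 5.3 points with odds ratio 3 (49.1% to 43.8%).

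**Step 3: bias, if caesarean use differs between groups (independent components).**

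| Assumed change with surgery | Composite, conservative | Composite, surgical |
|---|---|---|
| m 22% to 14%, c 40% to 50% | 53.2% | 1 − 0.50 × 0.86 = 57.0% |
| m unchanged at 22%, c 40% to 30% | 53.2% | 1 − 0.70 × 0.78 = 45.4% |

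In the first row complications fall but the composite rises. In the second nothing medical changes, yet the composite falls by 7.8 points, more than the 4.8 points from the genuine improvement in Step 2. With m falling from 20% to 15%, 30% to 22.5% or 30% to 20%, a rise in caesarean of 2.6 to 9.4 points is enough to cancel the gain.

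**Step 4: scale of the data.** Using "Natural conception based LBR of 1.4% per cycle has been reported" and the matching targets, the simulated 5 and 3 cycles, and at most one birth per woman:
- Conservative: 200 × (1 − 0.986^5) + 150 × (1 − 0.88^3) = 13.6 + 47.8, about 61.
- Surgical: 200 × (1 − 0.96^5) + 150 × (1 − 0.80^3) = 36.9 + 73.2, about 110.
- z without caesarean (22% against 14%): 0.08 / √(0.22 × 0.78/61.4 + 0.14 × 0.86/110.1) = 1.28.
- z with caesarean (53.2% against 48.4%): 0.048 / √(0.532 × 0.468/61.4 + 0.484 × 0.516/110.1) = 0.60.
- Counting every cycle instead gives 14 + 54 = 68 and 40 + 90 = 130 births, and z of 1.36 and 0.64.

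These counts treat simulation inputs as if they were follow-up and use births, whereas the outcome is defined among women who conceive. They show scale only.

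**The case against.** Several stronger readings are tempting, and the article does not support them.

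- *The composite mainly measures mode of birth.* A reader might infer this, but it needs rates that are not given. The caesarean-only share is one half or less in 7 of 24 assumed cells, so only the possibility of dominance is established.
- *The composite will make surgery look harmful.* That requires more caesareans after surgery, which is stated nowhere. The opposite bias is equally possible. With no group difference in caesarean use, the composite still moves in the right direction, only by less.
- *The definition contradicts the Introduction.* The list of complications there is introduced as examples, so the absence of caesarean is a mismatch with the rationale and not a contradiction.
- *This composite is the plan's test of whether surgery lowers obstetric risk.* The clinical pregnancy items say that groups will be compared; the obstetric item speaks only of rates, and the models described cover pregnancy and live birth. A comparison by management group is the natural use, given the question raised in the Introduction and Discussion, but no test is stated. Separate reporting of components may sit in documents not shown.
- *Removing caesarean would rescue a conclusion.* Both z values in Step 4 are well short of significance. The gain is in interpretation.

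Two further points stand in part. If complications lead to caesareans, fewer complications would also mean fewer caesareans, which would offset some of the dilution. Whether mode of birth belongs in such a composite is also to some extent a matter of preference. Neither explains why an uncomplicated planned caesarean should count as an adverse perinatal outcome, which is what the definition does.

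**Conclusion.** The concern holds in limited form. As written, an unqualified caesarean component may dominate the composite (caesarean-only share about 30–83%). With equal caesarean use, the composite retains between 45% and 75% of any fall in the other components (independent components assumed). If caesarean use differs between groups for non-medical reasons, the comparison can be biased in either direction, and a difference of 2.6 to 9.4 points is enough to cancel the plausible medical gains examined.

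All of these sizes rest on assumed component rates and, where stated, on independence. What rests on the text alone is that any caesarean counts, that it counts equally, and that it is not among the complications the article gives as its reason for studying obstetric outcome. This is a secondary outcome: the primary live birth comparison and the sample size are not affected.

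**What to change.** In Secondary outcomes, delete caesarean delivery from the composite and report it separately as mode of birth by management group. Split it into planned and emergency where the retrieved hospital records give this; the article does not show that caesarean type is collected, so the split should be conditional. Make the change before obstetric outcomes are compared by group.

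The cost is one line in the outcome definition. Mode of birth must already be obtained to score the composite as it stands, so reporting it separately needs no new item. The downside is fewer composite events: in the central example the rate drops from 53.2% to 22%. The 31.2 points lost (0.40 × 0.78) are women whose only event was a caesarean, and they do not bear on the question the Introduction asks.
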